**Fig. 1 Fig1:**
[figure not shown]
Study flow diagram

### Interventions

The interventions for the study will be PEM and PFMT. These training programmes will be administered by the researcher and four trained physiotherapists with postgraduate qualification in women’s health. Two research assistants will be attached to each of the two training groups (i.e. two for PEM and two for PFMT). All trainings in both groups will be carried out in the morning. Both training programmes are structured to conform to the Consensus on Exercise Reporting Template (CERT) checklist [39, 40].

## The Paula exercise method

The Paula exercise method will be adapted from previous studies where the method has been described in detail [27, 32]. No equipment will be needed for the exercise. The exercise will involve contracting and relaxing the eye muscles daily. The participants will first assume a comfortable sitting position on a chair (with back rest), and relax for two (2) minutes. The researcher or research assistance will teach the participant (until mastered) how to effectively contract (squeeze) the eye muscles and hold it for five (5) seconds, and then relax the muscles for three (3) seconds (this makes one exercise cycle). The exercise cycle will be repeated forty (40) times in a daily session. The same exercise procedure will be repeated daily by all the participants for twelve (12) weeks. The exercise procedure will be performed under the supervision of the researcher or any of the two research assistants during Week One of the study. Subsequently, participants will be instructed to continue with the exercise procedure at home for the remaining 11 weeks. Participants will each receive an activity log book in which to document their daily training activities (such as time training was performed and the duration of the activity) and any adverse event experienced during the training. The researcher and the research assistants will continually monitor the participants’ daily exercise performances through phone calls to ensure adherence. At four, eight and twelve weeks, each participant will be asked to visit the study centres (physiotherapy departments of either MMSH or JGH according to where the participant was recruited) to perform the exercise in group (according to the protocol specific for this group) in the presence of the researcher and/or research assistant and to re-assess the functional outcomes.

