## Background

Vesicovaginal fistula (VVF) is an abnormal opening between the vagina and the bladder that occurs often during childbirth as a result of prolonged obstructed labour [1, 2]. This occurs following compression on the pelvis by the foetal head resulting in tissue necrosis. This creates an opening between the vagina and bladder which leads to constant urine leakage from the vagina [1–3]. It is the major type of obstetric fistula, accounting for about 90% of all obstetric fistula cases [1, 4]. It is also regarded as one of the major causes of morbidity among females in developing countries and some parts of developed countries [2, 5]. The consequences of VVF can be devastating, as it affects women physically, socially, economically and psychologically [3, 4].

A number of studies have noted the risks for developing VVF as including: illiteracy, poverty or low socio-economic status, childbearing at an early age, lack of access to antenatal care, lack of skilled or trained traditional birth attendants, and a malformed pelvis [3–8]. Obstetric VVF affects 2 million women worldwide, with a prevalence of 3 per 1000 women in sub-Saharan Africa [2, 5, 8]. In Nigeria, according to the Federal Ministry of Health [9], there are over 20,000 new cases of VVF yearly, in addition to the approximately 400,000–800,000 existing cases awaiting surgical repair. Over 85% of all cases of VVF are found in the north-western part of Nigeria [7, 10]; high incidences are reported in Kano, Katsina and Bauchi states in this region of the country [7].

Surgical interventions have been proven to be the effective management for VVF, especially in complex fistula, and in small fistula if conservative treatment fails [1, 11]. Unfortunately, some women pass through the devastating period of having the VVF and undergoing the surgical procedure, but do not regain continence [1, 12, 13]. The VVF repair may be satisfactory anatomically, but inadequate functionally, as some women present with urinary leakage (called post-fistula repair incontinence) even after a successful repair [12–16].

Post-fistula repair incontinence (PFRI) as reported in the literature, is one of the most common complications of VVF surgeries, where urine continues to leak (especially with exertion) after successful VVF closure [12, 13, 17]. This incontinent gap is poorly understood and is a source of frustration to fistula surgeons (and particularly the patients) [1, 16, 18–20].

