## Methods

### Study design and sample

The research design for this study is a randomized controlled trial (RCT). It is a quantitative research in the form of pretest, posttest and follow-up design. The study will be a two-arm, outcome assessor-blinded RCT. The two-arms will comprise an intervention and a control. Following participants’ consent and baseline assessments, eligible participants shall be allocated randomly into either the intervention group (Paula exercise method) or the control group (pelvic floor muscle training). The proposed timeline for this study is 12 calendar months from participants’ enrolment to follow-up assessments; Table 1 below:

**Table 1 Tab1:** Study timeline from enrolment to completion

	Enrollment	Allocation	Post-allocation				Follow-up
Time point	− t	0	t0 (0 week)	t1 (4 weeks)	t2 (8 weeks)	t3 (12 weeks)	t4 (6 months)
Enrollment: eligibility screen informed consent allocation	X						
	X						
		X					
Intervention: Paula exercise (experimental group) Pelvic floor muscle training (control group)			X	X	X	X	
			X	X	X	X	
Assessments: baseline variables—age, weight, height, blood pressure, marital status, educational status, post fistula repair time	X	X					
Assessments: outcome variables [Primary outcome- urine leakage] [Secondary Outcome- pelvic floor strength, quality of life, sexual function, depression and anxiety]			X	X	X	X	X

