## Pelvic floor muscle training (PFMT)

The PFMT will be performed according to the clinical practice standard for pelvic floor exercise [27]. No equipment will be needed for the exercise procedure. The exercise will involve contracting (squeezing) and relaxing the PFM as if trying to stop urine from leaking or trying to raise the vagina up from the chair but, without contracting the abdominal, thigh, and buttock muscles. Each participant will be asked to comfortably lie supine on a bed (with knees in semi-flexed position) and relax for two (2) minutes before commencing the exercise. Each participant will receive detailed explanation on how to perform the exercise. Participants will then be asked to expose their vagina (to allow for visual assessment) and squeeze their PFM (as if trying to stop urination) and keep this position for a count of seven (7) and, then relax for a count of three (3). The researcher and/or the research assistant will observe the contraction of the PFM to ensure that the exercise is done correctly. Participants will be asked to use a mirror to accomplish biofeedback for better understanding and accuracy of the procedure [41]. The exercise will be repeated until mastered by the participant. The exercise will then be performed in a sitting position where each participant will assume a comfortable sitting position on a chair (with back rest) for two (2) minutes, and then perform the exercise procedure as explained above. The exercise will be performed forty (40) times during a session once daily. Participants will perform the procedure individually in the study centre (of either at MMSH or JGH) for the first week and under the supervision of the researcher and/or two (2) research assistants. Subsequently, participants will be asked to perform the exercise at home; the researcher or research assistants will track the participants’ individual daily exercise performance through phone calls to ensure adherence. Participants’ home-based activities (time and duration of training performed and any adverse event experienced) will be recorded daily in the activity log book which will be given to each participant. At four, eight and twelve weeks, each participant will visit the study centre (of either MMSH or JGH) to perform the exercise in group (according to the protocol specific for this group) in the presence of the researcher and/or research assistant and to re-assess the functional outcomes.

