In both study groups, a participant’s treatment will be terminated/discontinued if the patient: (1) decides to opt out of the study, (2) develops persistent vaginal bleeding, (3) presents with other medical emergencies or adverse events including life-threatening episodes (uncontrollable bleeding); incapacitation; readmission into hospital or incidence of a sudden collapse resulting in a medical emergency within 48-h would be rated as severe adverse episodes. However, minor adverse events would include bruise due to a scratch by exercise equipment, fall that does not result in loss of consciousness, fracture, admission into hospital, dyspnoea, cut, muscle soreness or pain persisting beyond 48 h, and sudden hypertension or hypotension interfering with the study flow for a day. Participants’ relations would be asked to document any such events within the period of the study and/or report such situation to the research team. Regular medical/surgical care being received by the patients, not involving exercise procedure of similar characteristics to this study exercise interventions would be allowed to continue for participants in both groups.

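### Adverse events are to be logged under different wording in the two arms and no active enquiry about harms is described, so recording may be incomplete or unequal (minor)

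*Protocol article*

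**What the plan says.** Three places in the protocol article govern how adverse events are recorded.

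- **The Paula exercise method.** "Participants will each receive an activity log book in which to document their daily training activities", together with "any adverse event experienced during the training".
- **Pelvic floor muscle training (PFMT).** The bracket that explains home-based activities reads "time and duration of training performed and any adverse event experienced". Entries are made every day, in a log book that all participants in this arm also receive.
- **The paragraph on discontinuation and adverse events that closes the PFMT section.** It opens by applying to both groups and lists severe and minor events. It then says that participants' "relations would be asked to document any such events within the period of the study", or report them to the research team.

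Staff contact during home training is described alike in both arms. Staff follow participants' "daily exercise performances through phone calls to ensure adherence" (Paula section; the PFMT section gives the same purpose). The visits at 4, 8 and 12 weeks are for supervised group exercise and re-assessment of functional outcomes. Nowhere does the article say that staff will ask about adverse events, and nowhere does it say that they will not.

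**The concern.** One instrument is used in both arms, but the instruction for its adverse-event entry is not the same. The qualifier that narrows it appears only in the experimental arm. If staff and participants follow the wording as printed, an event some hours after a session belongs in a PFMT participant's log and not in a Paula participant's log. The Interventions section attaches different research assistants to each arm, so a difference in wording could become a difference in practice.

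The routes described are also passive: a log kept by the participant, and reports from relatives. After the first week the training is done at home. What the team learns about harms, including the events that the article ties to discontinuation, then depends on someone choosing to write them down or report them. At stake are the completeness of the safety record and whether harms can be compared between arms. Events that were never elicited cannot be recovered after data collection.

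**Working it through.** The plan gives no figure on this point, so there is nothing to reproduce. The check sets the texts side by side, with a little arithmetic on time windows.

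**1. Windows as worded**
- Paula log: events during the training.
- PFMT log: any event, entered daily, within a bracket that explains home-based activities.
- Relatives, both arms: the listed events over the study period, which Table 1 extends to a 6-month follow-up.

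**2. Narrow reading of the Paula wording (one session)**
- Inputs from the Paula section: 5 s contraction, 3 s relaxation, 40 cycles, 2 min initial rest.
- 40 × (5 + 3) s = 320 s, about 5.3 min. With the rest, 320 + 120 = 440 s, about 7.3 min.
- The Randomization section says the Paula group also receives PFMT. Taking one count as one second (an assumption), that adds 40 × (7 + 3) = 400 s, so 320 + 400 = 720 s, or 12 min without rests.
- On any of these figures, soreness or pain lasting beyond 48 hours cannot fall inside a session, and readmission would not either. Both are on the article's own event list.

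**3. Broad reading (the 12-week programme)**
- The Paula log then covers the whole intervention period and the two arms hardly differ.

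**4. Which reading is meant**
- The sentence that sets up the Paula log also uses the word training for the daily activity whose time is to be written down. That favours the session reading.
- The Interventions section uses the same word for the whole programmes, which favours the broad one.
- The text does not settle it.

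**5. Reliance on passive routes**
- Home training: 11 × 7 = 77 of 12 × 7 = 84 days, 77/84 = 92%. Phone contact and the 4-, 8- and 12-week visits fall within or at the end of this time.
- The log is a training record for 12 weeks. If the 6-month visit is counted as week 26 from the start of training (an assumption), 26 − 12 = 14 weeks follow without it, 14/26 = 54%. This gap is the same in both arms, and over it relatives' reports are the only stated route.

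**6. Size of any under-count**
- This would need event rates and the share of events each route captures. The article gives neither, so no figure can be derived.

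**The case against.** The strongest case on the other side is that this is one loosely drafted phrase. Both arms use the same log book with the same kinds of entry. The PFMT wording does not say that the whole day is covered, so setting a few minutes against a full day would compare the narrowest reading of one arm with the widest reading of the other. The relatives' route applies to both groups over the study period, so a collapse or bleed later in the day in the Paula arm still has a stated way to reach the team. Harms are not among the study objectives or outcomes, and the Data analysis section plans no comparison of them. Call scripts and event forms may sit in the full protocol, which is not shown.

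Most of this stands, and it rules out several stronger readings that a reader might infer:

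- *That harms will certainly be biased in favour of the Paula method.* The broad reading and the common relatives' route both prevent that conclusion.
- *That participants report in one arm and relatives in the other.* Participants log in both arms and relatives report in both. The sources add to each other; what is missing is a statement of how they are combined.
- *That the calls exclude harms.* The article states a purpose for the calls and does not limit their content.
- *That a given share of events is lost because women cannot write the log.* The Background names "illiteracy, poverty or low socio-economic status" among risk factors for fistula, but gives no literacy figure for these participants, and relatives or staff could help.
- *That the event list conflicts with Table 1, which places blood pressure among the baseline variables.* The listed event is a sudden change that disrupts participation. It does not depend on scheduled readings.

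The objection does not remove the difference in wording. That is a matter of what the article states, not of detail left out. Nor does it explain how the session reading fits the article's own event list.

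**Conclusion.** The point holds as a minor one. The adverse-event wording differs between the arms. Read literally, the log window is narrower in the experimental arm and leaves out events that the article itself lists. If the training means the 12-week programme, the difference all but disappears. Separately, the stated routes are a self-kept log and relatives' reports, with adherence the only stated purpose of the calls. Events may therefore be under-recorded in both arms, or recorded unequally between them. No size can be attached, because the article gives no event rates. The conclusion rests on the article's text alone; a fuller protocol may already describe active enquiry, but it would still have to agree with these three passages.

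**What to change.** Reconcile the Paula section, the PFMT section and the paragraph on discontinuation and adverse events to one adverse-event definition and one window for both arms, from randomization to the 6-month visit. Have staff ask the same fixed adverse-event questions in both arms, about events since the last contact, and write down the answers. Do this at the phone calls already planned and at the 4-, 8- and 12-week and 6-month visits. Keep the log books and relatives' reports as supplements, and state how they are reconciled with the staff record.

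The cost is slightly longer calls and forms, and more minor events recorded. No extra visit is needed, and the sample size and planned analyses are unaffected.

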## Pelvic floor muscle training (PFMT)

The PFMT will be performed according to the clinical practice standard for pelvic floor exercise [27]. No equipment will be needed for the exercise procedure. The exercise will involve contracting (squeezing) and relaxing the PFM as if trying to stop urine from leaking or trying to raise the vagina up from the chair but, without contracting the abdominal, thigh, and buttock muscles. Each participant will be asked to comfortably lie supine on a bed (with knees in semi-flexed position) and relax for two (2) minutes before commencing the exercise. Each participant will receive detailed explanation on how to perform the exercise. Participants will then be asked to expose their vagina (to allow for visual assessment) and squeeze their PFM (as if trying to stop urination) and keep this position for a count of seven (7) and, then relax for a count of three (3). The researcher and/or the research assistant will observe the contraction of the PFM to ensure that the exercise is done correctly. Participants will be asked to use a mirror to accomplish biofeedback for better understanding and accuracy of the procedure [41]. The exercise will be repeated until mastered by the participant. The exercise will then be performed in a sitting position where each participant will assume a comfortable sitting position on a chair (with back rest) for two (2) minutes, and then perform the exercise procedure as explained above. The exercise will be performed forty (40) times during a session once daily. Participants will perform the procedure individually in the study centre (of either at MMSH or JGH) for the first week and under the supervision of the researcher and/or two (2) research assistants. Subsequently, participants will be asked to perform the exercise at home; the researcher or research assistants will track the participants’ individual daily exercise performance through phone calls to ensure adherence. Participants’ home-based activities (time and duration of training performed and any adverse event experienced) will be recorded daily in the activity log book which will be given to each participant. At four, eight and twelve weeks, each participant will visit the study centre (of either MMSH or JGH) to perform the exercise in group (according to the protocol specific for this group) in the presence of the researcher and/or research assistant and to re-assess the functional outcomes.

In both study groups, a participant’s treatment will be terminated/discontinued if the patient: (1) decides to opt out of the study, (2) develops persistent vaginal bleeding, (3) presents with other medical emergencies or adverse events including life-threatening episodes (uncontrollable bleeding); incapacitation; readmission into hospital or incidence of a sudden collapse resulting in a medical emergency within 48-h would be rated as severe adverse episodes. However, minor adverse events would include bruise due to a scratch by exercise equipment, fall that does not result in loss of consciousness, fracture, admission into hospital, dyspnoea, cut, muscle soreness or pain persisting beyond 48 h, and sudden hypertension or hypotension interfering with the study flow for a day. Participants’ relations would be asked to document any such events within the period of the study and/or report such situation to the research team. Regular medical/surgical care being received by the patients, not involving exercise procedure of similar characteristics to this study exercise interventions would be allowed to continue for participants in both groups.

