### Setting

All participants will be recruited from Murtala Muhammad Specialist Hospital (MMSH) and Jahun General Hospital (JGH) in Kano and Jigawa states of Nigeria respectively. The training will be conducted at the physiotherapy departments of the two institutions. The MMSH is a major health institution in Kano State; it is a specialist and referral centre to all hospitals in Kano State and its neighbouring states. It has a bed capacity of eight hundred and twenty six (826), thirty (30) wards and units, nine (9) operating theatres, fourteen (14) clinics, and a staff strength of 1656. Similarly, JGH is a state hospital located in Jahun local government area of Jigawa State. It provides quality health services to people in Jigawa State and the neighbouring states. It is a 300-bed capacity hospital with diverse clientele who receive treatment from the different clinical departments of the facility.

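### The adverse-event paragraph is ambiguous on hospital admission and fracture, contradicts itself on admission when read as a plain list, and merges severity grading with the rule for ending treatment

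*Protocol article*

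**What the plan says.** All the relevant text is in the last paragraph of the protocol article's section Pelvic floor muscle training (PFMT). It applies to both arms and does three things in succession.

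- **Ending treatment.** It opens with "In both study groups, a participant’s treatment will be terminated/discontinued if the patient" and gives three criteria: opting out, persistent vaginal bleeding, and a third that begins "presents with other medical emergencies or adverse events including life-threatening episodes (uncontrollable bleeding); incapacitation".
- **Severe class.** The same sentence continues, without a stop, to "readmission into hospital or incidence of a sudden collapse resulting in a medical emergency within 48-h would be rated as severe adverse episodes".
- **Minor class.** The next sentence opens with a contrast and lists minor events. It starts with a bruise from a scratch by equipment and goes on to "fall that does not result in loss of consciousness, fracture, admission into hospital, dyspnoea, cut, muscle soreness or pain persisting beyond 48 h", then to sudden changes in blood pressure that disturb the study for a day.

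Relatives are asked to document or report these events. The two intervention sections also have participants note adverse events in a daily log book.

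**The concern.** A grading rule has to put a given event in one class, whoever applies it. Here two adjacent sentences use nearly the same term, *readmission* in the severe class and *admission* in the minor list, and the minor list is punctuated so that its meaning depends on how far a negation reaches. Fracture stands next to admission in that list and shares the ambiguity.

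What is at stake is participant safety and the record of harms. The grading sits inside the rule for ending treatment, so an unclear grade can leave it unclear whether treatment continues. Under the Paula section, 11 of the 12 weeks of training take place at home, so many events will reach the team as reports from participants or relatives and will have to be classified afterwards from this paragraph.

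**Working it through.** No arithmetic applies: the point rests on no sample size, error rate or event count. The check is to read the paragraph under each reading that its grammar allows.

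**Step 1. How far the negation in the minor list reaches.** The phrase about the fall can govern one, three or all of the terms after it.

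| Reading | What the fall must not cause | Hospital admission | Fracture | Other terms |
|---|---|---|---|---|
| A, plain list | loss of consciousness only | minor, while readmission is severe | minor | dyspnoea, cut, soreness or pain: minor |
| B, negation covers three terms | loss of consciousness, fracture, admission | not in the minor list; no conflict | no named class | dyspnoea, cut, soreness or pain: minor |
| C, negation runs to the end of the phrase | every term up to the 48 hours | not in the minor list; no conflict | no named class | dyspnoea, cut, soreness and pain: no named class |

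Reading A is the plain one. A negated list would normally be closed by a conjunction before its last member, and none stands before the admission term. The only conjunction in the run comes between soreness and pain. Reading B gives better sense for a fall, but nothing in the text shows that the negation stops there. No reading gives a named class to every event in the paragraph without conflict.

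**Step 2. Admission against readmission.** The two words are not identical and neither is defined. All participants have already had a fistula repair, and the Participants section requires more than 3 months of incontinence after it. A new hospital stay could therefore be called either an admission or a readmission. The two terms overlap in this population, which is why Reading A produces a conflict.

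**Step 3. The 48 hours in the severe sentence.** It can qualify the collapse alone, in which case a readmission is severe whenever it occurs. Or it can qualify the readmission as well, in which case a later readmission falls outside the sentence. No starting point for the 48 hours is given under either reading.

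**Step 4. Grade and action.** The third criterion, "presents with other medical emergencies or adverse events including life-threatening episodes", names adverse events without limiting them to severe ones, so taken literally any adverse event could end treatment. The contrast that opens the minor-event sentence suggests that minor events are treated differently. The text does not say which is meant.

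**Step 5. Equipment.** The minor list includes a scratch from exercise equipment, while the Paula section states "No equipment will be needed for the exercise" and the PFMT section says the same of its procedure. This is a stray example that misclassifies nothing, so it is editorial.

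**The case against.** The strongest reply is that the minor sentence makes good sense as a fall without loss of consciousness, fracture or admission. On that reading admission is not a minor event and the contradiction is gone. Both lists are worded as examples, so an event that is not named is a gap and not a conflict, and incapacitation or a medical emergency would cover some fractures. The article also condenses a fuller protocol, and harms are not among its objectives, outcomes or planned analyses.

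Part of this stands. The double classification of admission holds under one reading only, and an unnamed class for fracture is a lesser fault than a contradiction. What does not stand is that the text settles the matter: it does not mark the end of the negation, and the plain list reading is at least as available as the benign one. Nor is this detail left to another document, since the rule is stated here and is unclear as stated.

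A reader might infer more than the text supports:

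- **That the two hospitals would grade differently.** One rule is given for both groups and nothing describes grading by site. The risk is between any two assessors.
- **That the same event would lead to opposite treatment decisions.** No separate action is stated for minor events, so the consequence for treatment is unknown.
- **That severity alone decides when treatment ends.** Opting out and persistent vaginal bleeding end treatment whatever the severity.
- **That a distorted severe-event rate can be calculated.** No reading puts fracture in the severe class, and no expected event count is given.

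**Conclusion.** The point holds in a limited form. The paragraph is ambiguous on hospital admission and fracture. On its plain list reading it contradicts itself on admission, and on the alternatives it leaves fracture without a named class. The reach of the 48 hours and the status of minor events under the third discontinuation criterion are also undetermined. Any two assessors following the text faithfully could grade the same event differently.

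In size, two event types are affected under every reading or under the plain one (fracture and admission respectively), and dyspnoea, cuts, soreness and pain join them under the widest reading of the negation. The effect is on safety management and the description of harms. There is none on the efficacy analysis, power or alpha.

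The conclusion assumes that a new hospital stay in a woman with a previous repair can be called either an admission or a readmission, since the article defines neither. It takes no view on which class any event belongs to.

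**What to change.** Rewrite the paragraph in three separate parts.

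1. **Severity grading.** Reconcile the severe and minor sentences so that each event sits in exactly one class. Say expressly where hospital admission, readmission and fracture belong, and give the fall its own item with its conditions closed off.
2. **The 48 hours.** State which events the limit in the severe sentence applies to and what it runs from.
3. **Ending treatment.** List the events that end treatment apart from the grading, and say whether events graded minor are only recorded or can also end treatment.

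The investigators and the ethics committees should decide the class of each event and which events end treatment. The equipment example can be removed in the same edit.

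The cost is small: one reworded paragraph, a matching change to the adverse-event page of the record form, and a minor protocol amendment. No design, sample-size or analysis element changes.
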